### Screening Assessment

The screening assessment will test for the inclusion criteria: (a) aged 18 years or older; (b) owner of a smartphone (Android or iOS) with mobile internet connection; and (c) interested and motivated to participate in a digital coaching to promote and strengthen self-control.

Moreover, we will screen for the two exclusion criteria: Participants will be asked whether they currently are in psychotherapeutic or psychiatric treatment. Also, the Depression Scale [ADS-K; (49)] will be used to assess mental health problems. Individuals with scores above the cut-off value in the ADS-K (≥19) will be excluded and are provided with information and contact details of the psychological counseling service of the University of Zurich for appropriate treatments and they can also contact the study office for more information.

### Primary Outcome Self-Report Assessment

The Self-Control Scale [SCS; (10)] will be used to measure individual differences in the ability to control impulses. The self-discipline facet scale from the International Personality Item Pool [IPIP; (50, 51)] will be used. The conscientiousness scale from the Big Five Inventory-2 [BFI-2; (52)] will be used to measure individual differences in conscientiousness. These self-report measures will be used at pre-test, post-test and follow-up assessment.

### Secondary Outcome Self-Report Assessment

The other Big Five traits will be measured using the BFI-2 (52) to examine potential transfer effects of the digital coaching on personality traits other than conscientiousness. Satisfaction with life in general will be assessed using the Satisfaction with Life Scale [SWLS; (53)] and single-item measures to assess satisfaction with health, work, and relationships. Finally, the Rosenberg Self-Esteem Scale [RSES; (54)] will be used to assess individual differences in self-esteem.

### Outcome Observer Reports Assessment

In addition to self-reports, observer reports by close others will be used. At the beginning of the study, participants will be asked to share a link to the online observer report questionnaires with at least three close friends, family members, or their intimate partner. Observer reports include the SCS (10) and a short form of the BFI-2 [BFI-2-S; (55)], type and closeness of the relationship and time spent with the target person. A short version of the Behavioral Indicators of Conscientiousness [BIC; (56)] will be used to rate observable conscientious behaviors. Observer reports will be assessed at pre-test, post-test, and follow-up assessment.

### Process Self-Report Assessment

During the 7-week intervention, there will be weekly assessments of the SCS (10) every last day of the week. The instruction will be: “For each statement, indicate how much it applied to you in the past week.” Additionally, 1 day after each practice session, participants will be asked (a) whether they completed the task (yes, no); (b) if not, why they could not complete the task (no time, task not understood, no desire, other reasons); (c) whether they could learn anything from the task (ranging from “little” to “a lot”) and (d) how difficult the task was for them (ranging from “simple” to “difficult”).

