## Methods and Analysis

### Study Design

A single-arm study design with repeated measures will be used to evaluate the 7-week digital coaching to promote self-control (49 days). Single-arm trials, in which all participants are enrolled in the same treatment, are common in the first phases of the evaluation process of a treatment and are characterized by an exploratory nature. The current study is not designed to obtain definitive conclusions about the effectiveness of the digital intervention but rather to provide initial evidence. Outcome assessments will be completed at pre-test, at the end of the coaching (~8 weeks later), and at the 2-month follow-up after the coaching (~16 weeks after start of the study). Moreover, intensive longitudinal assessments will include end-of-week and daily assessments during the 7-week intervention phase. The design and procedure of the study is shown in Table 1.

**Table 1 T1:** Design and procedure of the study.

**Pre-test (T1)**	**Intervention**	**Post-test (T2)**	**Follow-up (T3)**
**Day 0 (week 1)**	**Day 1–49 (week 1–7)**	**Day 50 (week 8)**	**Day 106 (week 16)**
*Self-reports*	*Daily coaching session*	*Self-reports*	*Self-reports*
–Primary outcome assessment	–At individually preferred time	–Primary outcome assessment	–Primary outcome assessment
–Secondary outcome assessment	*Self-reports* –Process assessment	–Secondary outcome assessment	–Secondary outcome assessment
*Observer reports*		*Observer reports*	*Observer reports*
–Outcome assessment		–Outcome assessment	–Outcome assessment

*The pre-test (T1) will also include the informed consent and the screening assessment*.

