### Procedure

The procedure of the study is shown in Table 1. After giving informed consent and passing the screening assessment, participants will be directed to the pre-test assessment. After having completed the pre-test assessment, participants will download and install the mobile application and will start with the first app-based coaching session. The duration of the intervention is 7 weeks. At every last day of each week, participants will be asked to complete a short self-control measure. After the intervention, participants will be asked to complete the post-test assessment and then after 2 months, participants will be contacted to complete the follow-up assessment (Table 1). To reduce the risk of missing data, an online survey platform (https://www.unipark.com/) external to the MindHike application will be used to obtain informed consent and to assess the outcome variables. Online survey platforms provide “force response” options which require the respondents to answer questions before they can continue the survey. The weekly process assessments will be completed using the MindHike app.

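### The weekly past-week SCS has no pre-coaching value, so the weekly series starts on Day 7 and cannot by itself show change in week 1

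*Protocol article*

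**What the plan says.** Under Process Self-Report Assessment, the protocol article plans the weekly measure as follows: "During the 7-week intervention, there will be weekly assessments of the SCS (10) every last day of the week". Its instruction reads: "For each statement, indicate how much it applied to you in the past week".

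Under Study Design, the timing is confined to the coaching period: "intensive longitudinal assessments will include end-of-week and daily assessments during the 7-week intervention phase". Table 1 lists the process assessment only in the intervention column (Days 1 to 49), not at Day 0. Under Procedure, participants install the app after the pre-test. The weekly measure is completed in the app, and the outcome measures on a separate survey platform.

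The outcome SCS is described by its construct, as a scale that "will be used to measure individual differences in the ability to control impulses". Its timing is given by "These self-report measures will be used at pre-test, post-test and follow-up assessment", which Table 1 places at Days 0, 50 and 106. No instruction or reference period is given for it.

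Under Aims and Hypotheses, the second aim concerns within-person processes. Its first three hypotheses relate tasks accomplished, task difficulty and learning to increases in self-control.

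**The concern.** The pre-test and post-test give one change score per person. The weekly SCS is the only planned self-control series dense enough to ask whether a person's self-control rises more in weeks when more tasks are done or more is learned. To use week 1 in that analysis, one needs a score on the same form from before week 1.

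The first weekly score looks back over Days 1 to 7, all of them coaching days. By then the goal-setting, mental-contrasting and strengths tasks have been delivered. The study has a single arm, so a pre-coaching value is the only reference for change. If self-control improves early, the weekly series starts from a level that is already raised, and its slope understates the total change. If an analyst fills the gap with the pre-test SCS, any difference between the two administrations enters as week-1 change.

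**Working it through.** **1. The plan's own figure.** Inputs from Power Analysis: alpha 0.05, power 0.80, three assessments, correlation 0.40, d = 0.24, N = 136. With f = d/2 = 0.12, sphericity assumed, and noncentrality λ = n·m·f²/(1 − ρ):

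- λ = 136 × 3 × 0.0144 / 0.60 = 9.79, with 2 and 2 × 135 = 270 degrees of freedom.
- Power = 0.802, and 136 is the smallest n that reaches 0.80. At n = 150, power is 0.842.

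The stated sample size reproduces. It concerns the three outcome occasions, and the present point does not depend on it.

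**2. Coverage of the weekly series.** The last days of the seven weeks are Days 7, 14, 21, 28, 35, 42 and 49.

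| | As planned | With a Day 0 value |
|---|---|---|
| Values | 7 | 8 |
| Intervals | 6 | 7 |
| Coaching days spanned | 49 − 7 = 42 of 49 | 49 of 49 |

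**3. Process data in week 1.** Practice sessions in Table 2: 3 in the introduction, 4 in each of five strategy weeks and 5 in the closing week, so 3 + 5 × 4 + 5 = 28. Those on Days 3, 5 and 7 belong to week 1: 3/28 = 11%. They are rated one day later, on Days 4, 6 and 8, so 2 of 28 ratings (7%) are made by Day 7. None of the three sessions has an earlier weekly score from which to compute a change.

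**4. How much of the gain could precede Day 7.** The article does not give the shape of change, so three shapes are assumed, each with a total gain of d = 0.24 from Day 0 to Day 49. The share before Day 7 is s, and the change visible from Day 7 to Day 49 is 0.24 × (1 − s).

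- Linear: s = 7/49.
- Exponential with time constant τ days: s = (1 − exp(−7/τ)) / (1 − exp(−49/τ)).

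The last column is the power of a two-sided paired t-test at n = 150 and α = 0.05, with dz = d/√(2(1 − 0.40)) and noncentrality dz·√150. It assumes the same correlation of 0.40 between Days 7 and 49. For the full change, dz = 0.24/1.095 = 0.219, the noncentrality is 2.68 and power is 0.76.

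| Shape (assumed) | s | Visible d | Power |
|---|---|---|---|
| Full change, Day 0 to 49 | – | 0.24 | 0.76 |
| Linear | 14% | 0.21 | 0.63 |
| Exponential, τ = 14 | 41% | 0.14 | 0.35 |
| Exponential, τ = 7 | 63% | 0.09 | 0.17 |

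This is a two-point illustration of attenuation. It is not the power of the planned growth models, nor of the tests of the process hypotheses.

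**The case against.** **The pre-test SCS could serve as week 0.** Both administrations cite the same scale, and the article does not say that their instructions differ. A reader might infer that the two series cannot be joined. The documents do not support that: the pre-test instruction is simply not given. The Day 49 weekly score and the Day 50 post-test are one day apart, so the forms could be linked if their relation is assumed constant over time. What stands is that a link needs such an assumption, and nothing before coaching would test it.

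**The article plans no such join.** This is correct. Statistical Analysis announces separate models and does not mention pooling the weekly scores with the pre-test. Form change counted as coaching effect is therefore a risk to avoid, not an error in the stated plan.

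**The article may contradict itself on the weekly form.** Under Procedure, "participants will be asked to complete a short self-control measure"; elsewhere the weekly measure is the SCS. A reader might infer two item sets. But the word can mean brief compared with the pre-test battery, and no second item set is mentioned. This is not a clear contradiction.

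**The process hypotheses do not need the weekly series.** This is partly correct. Total tasks, difficulty and learning can be related to person-level change from Day 0 to Day 50, which includes week 1. The fourth process hypothesis needs the outcome occasions in any case, because self-reported conscientiousness is taken only then. But one change score per person supports a between-person association, whereas the stated aim is within-person.

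**Little is lost in week 1.** The five strategy groups start on Day 8, and week 1 is introductory. One could instead count microinterventions (3 of 13, or 23%) or suppose that half the gain comes in week 1. The first is not the unit in which the process predictors are collected, and the second has no basis in the article. The figures of 11% of sessions, and 14% of the gain under linear change, are the fairer ones.

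**The study is exploratory, and a series starting at the end of week 1 is a legitimate choice.** This also stands, provided that the conclusions are worded to match.

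**Conclusion.** The point holds in a limited form. The schedule and instruction that the article states leave no pre-coaching value on the past-week SCS. The weekly series alone therefore describes change from Day 7 to Day 49 and gives no week-1 increase to relate to week-1 tasks. Models built only on the weekly scores lose one of seven intervals and 3 of 28 practice sessions. Under linear change they also miss about 14% of the gain; a larger share requires front-loaded change, which is an assumption.

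It does not follow that week-1 change is lost to the study. The outcome hypotheses use Days 0, 50 and 106, and person-level pre-post process analyses still include week 1. This is a cheap design improvement, not the repair of a contradiction. It is worth deciding before enrolment, because a pre-coaching value cannot be obtained from a participant once coaching has begun.

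**What to change.** Add the weekly form to the Day 0 survey, with the same items and the same past-week instruction, and use it as week 0 of the weekly growth models. State the item set of the weekly form once, so that its wording under Procedure and under Process Self-Report Assessment is read the same way. The cost is one more short questionnaire in a survey that participants already complete, a few minutes before Day 1. The Day 0 value would be collected on the survey platform and the later ones in the app, a remaining difference in mode that should be noted.

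If the form is not added, state that the weekly models describe change from Day 7 onward and limit their conclusions accordingly. If the pre-test SCS is nevertheless used as week 0, give both instructions and state the equivalence or linking assumption. This costs only wording.

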### Statistical Analysis

Missing data analysis will be performed and the type of missing data (i.e., random or non-random) will guide the handling of missing data (e.g., data imputation, estimation techniques). Longitudinal multilevel modeling and longitudinal structural equation modeling will be used to analyze the longitudinal, nested data structure and change over time (57–59). Both data analytic methods are specifically suitable to model change explicitly as a function of time and can be used to formulate equivalent models, providing identical estimates for the collected data. Both methods include estimation procedures in which imputation of missing data is not necessary. Separate models will be analyzed including the outcome assessments at pre-, post- and follow-up (self-reports and observer reports), and the outcome self-report assessments. Predictor/control variables will be added to the models to examine how individual growth will be moderated by variables such as demographic variables. The statistical modeling programs Mplus (60), and updated R packages (R Core Team, Vienna Austria) will be used to estimate the growth curve models.

### Power Analysis

To assure adequate power for the primary outcome hypotheses, we calculated the sample size for a traditional ANOVA with repeated measures, within factors using the G^*^Power program (61). Assuming an α error level of 0.05, a statistical power (1-β) of 0.80, three assessments, and a correlation of 0.40 between the assessments, a sample size of at least 136 participants is required to detect a small effect (Cohen's *d* = 0.24). Computing power for longitudinal multilevel analyses and longitudinal structural equation models, which is the case in this study, is more complex. As such, this power analysis only gives a rough overview of the required sample size. Therefore, the sample will include at least 150 participants. We will over recruit participants (+25%) to be prepared for potential dropouts over time. Should drop-out rates be higher than expected, we may recruit additional participants to ensure sufficient statistical power.

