### Aims and Hypotheses

The first aim of the study is to examine the effectiveness of the digital coaching intervention to promote self-control. The focus of this initial research is on the within-person evaluation of the effectiveness of the digital coaching and not on the between-person comparison with active or passive control groups. As a first step in the evaluation process, this study will focus on a non-clinical sample of people without mental health conditions. The first outcome hypothesis is that participation in the digital coaching would lead to increases in self-control. The second outcome hypothesis is that participation in the digital coaching would also lead to increases in conscientiousness. The third outcome hypothesis is that participation in the digital coaching would lead to increases in satisfaction with life in general and satisfaction with health, work, and relationships, depending on the selected target area of the coaching (i.e., health, work, relationships, other) and the individual intervention goal.

The second aim is to examine underlying within-person processes and mechanisms that improve the outcomes of the digital coaching to promote self-control. The first process hypothesis is that the amount of accomplished tasks is positively related to increases in self-control. The second process hypothesis is that the difficulty of tasks is negatively related to increases in self-control. The third process hypothesis is that the amount of learning is positively related to increases in self-control. The fourth process hypothesis is that increases in self-control are related to increases in conscientiousness.

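### The Power Analysis labels the effect detectable with 136 participants as Cohen's d = 0.24, but 136 is the answer for f = 0.12, which with three assessments means a largest mean difference of about d = 0.25 to 0.29

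*Protocol article*

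**What the plan says.** The Power Analysis section of the protocol article says "we calculated the sample size for a traditional ANOVA with repeated measures, within factors using the" G*Power program. The inputs are "Assuming an α error level of 0.05", "a statistical power (1-β) of 0.80" and "three assessments, and a correlation of 0.40 between the assessments". The result is that "a sample size of at least 136 participants is required to detect a small effect (Cohen's *d* = 0.24"). The effect size f is not given.

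The section then notes that power for the multilevel and structural equation models actually planned is harder to compute, and treats the ANOVA figure as a rough guide. It sets the target at no fewer than 150, adds 25% over-recruitment for dropout, and allows further recruitment if dropout is higher than expected. The section on participants and recruitment counts the 150 as people who complete both post-test and follow-up. The hypothesis that heads the list is that "The first outcome hypothesis is that participation in the digital coaching would lead to increases in self-control".

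**The concern.** For this procedure the effect size is f, the standard deviation of the assessment means divided by the within-assessment standard deviation. The article reports Cohen's d instead. The two are linked by d = 2f only when there are two means, and the same sentence specifies three. If the reported d was obtained by doubling f, the stated detectable effect is smaller than the one that 136 participants detect with 80% power.

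At stake is how the sensitivity of the study is described. A published power statement is likely to be reused when the result is interpreted and when the controlled trials that the Discussion calls for are planned.

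**Working it through.** **Inputs, all from the Power Analysis section:** one group, m = 3 assessments, correlation r = 0.40, α = 0.05, power 0.80, stated N = 136, stated d = 0.24, planned N = 150. Sphericity (ε = 1) is not stated. It is assumed here because, with f = 0.12, it is the value that returns 136; ε = 0.75 would give 166.

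**Step 1. Reproduce the stated N.** For a one-group within-factors ANOVA the noncentrality is λ = f² × N × m / (1 − r), with df 2 and 2(N − 1). With f = 0.24/2 = 0.12 and N = 136:

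λ = 0.0144 × 136 × 3 / 0.60 = 9.79, power 0.802.

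At N = 135, power is 0.799. So 136 is the smallest N reaching 80% for f = 0.12. Other readings do not return 136:

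| Reading | N for 80% |
|---|---|
| f = 0.24 entered directly | 35 |
| Two assessments, f = 0.12 | 166 |
| Two-sided paired t, d = 0.24 taken as d_z | 139 |
| Effect size specified as in SPSS, f = 0.12 / 0.24 | 338 / 87 |

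**Step 2. Convert f to d for three means.** Let d be the largest standardized difference among the three means.

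- Two means equal, for example (0, d, d): f = d × √2/3 = 0.471d. This is the largest f that a given d can produce.
- Equally spaced means, for example (0, d/2, d) or a half-lost gain (0, d, d/2): f = d/√6 = 0.408d. This is the smallest.

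So f = 0.12 corresponds to d = 0.12/0.471 = 0.255 up to d = 0.12/0.408 = 0.294. Conversely, d = 0.24 gives f = 0.113 at most and 0.098 at least.

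**Step 3. Omnibus power for d = 0.24 at r = 0.40.**

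| Pattern of means | f | Power, N = 136 | Power, N = 150 | N for 80% |
|---|---|---|---|---|
| (0, d, d), gain kept | 0.113 | 75.1% | 79.4% | 153 |
| (0, d/2, d) or (0, d, d/2) | 0.098 | 61.8% | 66.4% | 203 |

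Simulation with 10,000 data sets per cell agreed: 75.4% and 62.2% at 136, 79.3% and 65.8% at 150.

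**Step 4. Contrasts, for context.** The hypothesis concerns an increase, so single-df comparisons are also informative.

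- Pre-test against post-test, two-sided: d_z = 0.24/√(2 × 0.60) = 0.219. Power is 71.8% at 136 and 76.0% at 150. The d detectable with 80% power is 0.265 at 136 and 0.252 at 150.
- Pre-test against the mean of post-test and follow-up: the variance of the difference is 1 + (1 + 0.40)/2 − 2 × 0.40 = 0.90. For a kept gain, d_z = 0.24/√0.90 = 0.253, and power is 83% at 136 and 87% at 150. For a half-lost gain the mean difference is 0.18, and power at 150 is 64%.

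**The case against.** There is a good case for treating this as small.

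- **d may be shorthand for 2f.** Then the computation is right and only the label is loose. This stands as an explanation of how the figure arose. But the text says Cohen's d, never gives f, and will be read as a standardized mean difference.
- **d may not be the largest difference.** If d is the pre-to-post change and follow-up rises slightly further, with means (0, 0.24, 0.267), f is 0.12 and power at 136 is 80.2%. It would therefore be too strong to say that 0.24 is an impossible value under every definition. That statement needs d to be the largest of the three differences, and the article does not define it. Nor does it state any pattern of means that would justify 0.24.
- **The plan has a margin.** With 150 completers and a kept gain, omnibus power for d = 0.24 is 79.4%, in effect the stated 80%. This stands. It does not cover a linear or half-lost gain (66%), and the Discussion itself leaves open whether gains will persist or revert.
- **The calculation is described as approximate.** That caveat concerns ANOVA as a stand-in for multilevel and structural equation models. It does not warn that the effect size is mislabelled within the ANOVA.

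Two stronger readings are tempting. A reader might infer that the study is underpowered, or that a null result would be misread as ruling out d = 0.24. The documents do not support either. The Study Design section calls the work exploratory and disclaims definitive conclusions. A contrast using both later assessments has 83% power at 136 for a kept gain. With r = 0.5 instead of 0.40, pre-post power at 150 would be 83%. A reader might also infer that the sample size must be based on the pre-post contrast. That is a preference: the planned models use all three assessments.

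**Conclusion.** The point holds as a mislabelled effect size, and it is minor. The stated N of 136 is correct for f = 0.12; reporting this as d = 0.24 applies a two-mean conversion to a three-mean design. The understatement of the detectable difference is 0.255 − 0.24 = 0.015 for a fully kept gain and 0.294 − 0.24 = 0.054 for a linear or half-lost one. In power terms, the claimed 80% at 136 is 75% to 62%.

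The conclusion assumes that d means the largest standardized difference among the assessment means, and it takes the article's r = 0.40, α = 0.05 and the omnibus test, with sphericity. It does not show that the sample is inadequate or that the design or analysis needs to change.

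**What to change.** In the Power Analysis section, replace d = 0.24 with the effect size actually used and its meaning for three assessments. For example: 136 participants give 80% power for f = 0.12, which with three assessments corresponds to a largest standardized mean difference of about d = 0.25 if the gain is fully kept at follow-up, and about d = 0.29 if the gain is linear or half lost.

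Optionally, add that with 150 completers and r = 0.40 the pre-to-post comparison has 80% power for d of about 0.25.

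The cost is a sentence or two of wording and a slightly less favourable stated effect. The target of 150 and the over-recruitment stay as they are. Keeping d = 0.24 with 80% omnibus power would instead need 153 to 203 completers, depending on the pattern of means, which is why correcting the label is the cheaper course.
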